### Causal relationship between surgery and adverse events

The causal relationship between the drugs used and AE will be evaluated by the researchers as: certainly relevant, probably relevant, likely relevant, unlikely relevant and irrelevant (table 4).

**Table 4 T4:** Causal relationship between surgery and adverse events

	Certainly relevant	Probably relevant	Likely relevant	Unlikely relevant	Irrelevant
Adverse events are obviously caused by external factors	-	-	-	-	+
Adverse events are correlated with surgical treatment at rational time	+	+	+	-	-
Adverse events are correlated with patient diseases	-	-	+	+	+
Adverse events are correlated with suspected postoperative response patterns	+	+/-	+	-	-
After relief of related surgical factors, adverse events alleviate or disappear	+	+	-	-	-
After surgery-related factors worsen, adverse events recur	+	+	-	-	-

To minimise the surgical risk and meet the requirements of laws and regulations, the sponsor will manage the correlations as follows: ‘Irrelevant’ belongs to the irrelevant category, and ‘certainly relevant’, ‘probably relevant’, ‘likely relevant’ and ‘unlikely relevant’ belong to the relevant category.

### Evaluation criteria for the severity of adverse events

Mild: The patient is aware of symptoms, but symptoms can be tolerated. Symptoms are causing mild discomfort but not interfering with daily activities.

Moderate: Not affecting daily activities.

Severe: Very painful, causing significant functional impairment or loss of self-care ability and prohibiting the patient from carrying out daily activities.

The researcher will evaluate the severity of AE according to clinical indices such as laboratory and inspection outcomes, not just based on the subject’s direct feelings.

### AE reporting

Reporting time limit for AE will be within 24 hours of onset. In the clinical research period (from the time of signing informed consent to 1–2 years postoperatively), any AE occurring in any patient who received either surgical approach will be properly treated. According to the requirements of this study protocol and clinical evaluation, researchers will fill in the table of Adverse Events After Herniorrhaphy and submit this within 24 hours to the Clinical Research Center of Abdominal Wall Hernia, the Fourth Affiliated Hospital of China Medical University, China.

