### Follow-up

Visit 3 (1 week after surgery via clinic visit or telephone follow-up)36-Item Short Form Health Survey (SF-36) score;Medical costs;Hernia recurrence (date and severity of recurrence). Recurrence will be diagnosed by the medical institutions, after being alerted by patients that symptoms are present.Presence or absence of haematoma and/or seroma;Wound infection (date and severity of wound infection).

Visit 4 (1 month after surgery via clinic visit or telephone follow-up)SF-36 score;Medical costs;Hernia recurrence (date and severity of recurrence). Recurrence will be diagnosed by the medical institutions, after being alerted by patients that symptoms are present.Presence or absence of haematoma and/or seroma;Wound infection (date and severity of wound infection).

Visit 5 (3 months after surgery via clinic visit or telephone follow-up)SF-36 score;Medical costs;Hernia recurrence (date and severity of recurrence). Recurrence will be diagnosed by the medical institutions, after being alerted by patients that symptoms are present.Presence or absence of haematoma and/or seroma;Wound infection (date and severity of wound infection).

Visit 6 (1 year after surgery via telephone follow-up)VAS pain score;SF-36 score;Medical costs;Hernia recurrence (date and severity of recurrence). Recurrence will be diagnosed by the medical institutions, after being alerted by patients that symptoms are present;Presence or absence of haematoma and/or seroma;Wound infection (date and severity of wound infection).

Visit 7 (2 years after surgery via telephone follow-up)VAS pain score;SF-36 score;Medical costs;Hernia recurrence (date and severity of recurrence). Recurrence will be diagnosed by the medical institutions, after being alerted by patients that symptoms are present;Presence or absence of haematoma and/or seroma;Wound infection (date and severity of wound infection).

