#### Secondary outcome measures

Postoperative complications including wound infection, rates of haematoma, seroma, hernia recurrence, intestinal obstruction, intestinal fistula, entocele, mesenteric thrombosis, femoral vein thrombosis, ischaemic orchitis, painful ejaculation, varicocele and scrotal oedema at postoperative 1 week, 1 and 3 months and 1 and 2 years.

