#### Other outcome measures.

Quality of life is evaluated by the SF-36.^21^The SF-36 is a 36-item, patient-reported survey of patient health. It consists of eight scaled scores, including vitality, physical functioning, bodily pain, general health perceptions, physical functioning, emotional functioning, social functioning and mental health. The score of each scale is summed and then standardised according to the formula: standardised score = (actual raw score—lowest possible raw score)/possible raw score range×100. The total SF-36 score is the standardised score based on the sum of the eight scaled scores. A higher score indicates better quality of life.

The cost utility analysis of therapeutic regimens involving different surgical approaches will be analysed. Medical costs consist of direct medical and non-medical costs. The direct medical costs include drug charges, inspection fees, laboratory fees, treatment fees, nursing fees and bed charges. The direct medical costs during hospitalisation will be calculated according to the hospital information system. Direct medical costs during the follow-up period will be reported by patients and/or their relatives. Direct non-medical costs include payments for transportation to receive medical care, cost of nutritional supplementation and the costs for accompanying family members during the treatment period.

All outcome evaluations will be independently performed by an experienced assessor blinded to the treatment regimens. The schedule of outcome measurement assessment is shown in table 3.

**Table 3 T3:** Timing of outcome measurement assessment

	Before surgery	During surgery	Follow-up				
	Visit 1 (at admission, day 0)	Visit 2 (at discharge)	Visit 3 (1 week after surgery)	Visit 4 (1 month after surgery)	Visit 5 (3 months after surgery)	Visit 6 (1 year after surgery)	Visit 7 (3 years after surgery)
Signed informed consent	X						
Inclusion/exclusion criteria	X						
Demographic data	X						
Medical insurance type	X						
Delayed visit and admission	X						
Previous history of diseases	X						
Previous history of drug	X						
Risk factors	X						
Disease attack and admission *	X						
Type of hernia (indirect hernia, direct hernia)	X						
Vital sign†	X						
Laboratory examination ‡	X	X					
Imaging examination §	X						
Electrocardiography	X						
Treatment regimen ¶		X					
VAS score **						X	X
SF-36 score			X	X	X	X	X
Medical cost		X	X	X	X	X	X
Concomitant treatment	X	X					

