Adverse events Wound infection Haematoma Seroma Hernia recurrence		X	X	X	X	X	X

*Indicates the interval from the first appearance of the lump or main symptoms.

†Indicates body temperature, pulse, respiration rate, and blood pressure.

‡Indicates routine blood testing, coagulation testing, testing of blood glucose, lipids and electrolytes and hepatic and renal function.

§Indicates ultrasound, CT examination.

¶Indicates inguinal hernia-specific treatment.

**Indicates the VAS pain score.

SF-36, 36-Item Short Form Health Survey; VAS, Visual Analogue Scale.

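### The adverse-event period ends at a variable 1–2 years, while complications are an outcome to 2 years, so nine complications not named at any visit may be under-counted

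*Protocol article*

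**What the plan says.** Under AE reporting, the protocol article defines the clinical research period as running "from the time of signing informed consent to 1–2 years postoperatively". It does not say who is followed for 1 year and who for 2. The next sentence tells researchers to complete the adverse-event form and submit it within 24 hours.

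Under Secondary outcome measures, 13 complications are an outcome "at postoperative 1 week, 1 and 3 months and 1 and 2 years". Four of them (wound infection, haematoma, seroma, recurrence) also appear in the visit lists. The other nine are "intestinal obstruction, intestinal fistula, entocele, mesenteric thrombosis, femoral vein thrombosis, ischaemic orchitis, painful ejaculation, varicocele and scrotal oedema".

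The Follow-up section ends with "Visit 7 (2 years after surgery via telephone follow-up", where the complications asked about are recurrence, haematoma or seroma, and wound infection. Table 3 has a row reading "Adverse events Wound infection Haematoma Seroma Hernia recurrence", marked from discharge to Visit 7, but its column heading is "Visit 7 (3 years after surgery".

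Under Patient completion/withdrawal, at least 1 year of data makes a complete case. The section on ethics and dissemination expects recruitment to finish by December 2019 and data collection by June 2020. The Statistical analysis section compares complication incidence between groups by the χ² or Fisher's exact test.

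**The concern.** A 2-year incidence needs a 2-year observation window in each patient, or an analysis that allows for shorter windows. The article fixes the outcome at 2 years in one place and leaves the end of the adverse-event period open between 1 and 2 years in another. For the four complications asked about at the last visit this matters little. For the other nine, the adverse-event form is the clearest route into the data, so its window largely determines what is counted.

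If some centres or patients stop at 1 year, a simple proportion mixes 1-year and 2-year risks under a 2-year label. Rates come out too low, cannot be compared with rates from trials that followed everyone for 2 years, and late safety events may be missed. With fewer events counted, a late difference between the approaches is also harder to see.

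**Working it through.** The plan gives no figure on this point to reproduce. The check is a comparison of sections, followed by two calculations whose assumptions are stated.

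**1. Which complications depend on adverse-event reporting**

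| Complications | Named at the 2-year visit | Named in Table 3's adverse-event row | Outcome at 2 years |
|---|---|---|---|
| Wound infection, haematoma, seroma, recurrence (4) | yes | yes | yes |
| Intestinal obstruction, intestinal fistula, entocele, mesenteric thrombosis, femoral vein thrombosis, ischaemic orchitis, painful ejaculation, varicocele, scrotal oedema (9) | no | no | yes |

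So 13 − 4 = 9 complications have no named item at any visit.

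**2. Could observation differ between patients in practice?**

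Inputs: start on 6 February 2017 (Abstract); recruitment to December 2019 and data to June 2020 (Ethics and dissemination); 720 patients (Sample size). Assumptions: uniform accrual, month-end dates, no loss to follow-up.

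- Accrual window: 6 February 2017 to 31 December 2019 = 1,058 days.
- 2 years reachable by 30 June 2020 if operated on by 30 June 2018: 509/1,058 = 48%, about 346 patients.
- Between 1 and 2 years: 365/1,058 = 34%, about 248 patients.
- Less than 1 year: 184/1,058 = 17%, about 125 patients.

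On the article's own calendar, therefore, about half the patients could not be observed for 2 years, whatever the AE reporting section says.

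**3. Form of the loss**

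Let R be the true 2-year risk, q the share of those events arising in year 2, and f the share of patients reported on for 1 year only.

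- Observed risk = (1 − f)·R + f·R·(1 − q) = R·(1 − q·f).
- Share of events lost = q·f.

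The documents give neither q nor f. As illustrations only:

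- q = 5%, f = 25%: 0.05 × 0.25 = 1.25% lost.
- q = 20%, f = 50%: 0.20 × 0.50 = 10% lost.
- q = 50%, f = 100%: 0.50 × 1.00 = 50% lost. This is the extreme at which everyone stops at 1 year.

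The width of the range shows that the documents do not determine the size.

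**The case against.** The best defence is that the range is loose shorthand for follow-up at the two late visits. Its sentence concerns the treatment of adverse events, and the sentences on reporting carry no end date. Table 3 marks adverse events at Visit 7, and the Secondary outcome measures section itself sets a 2-year time point. A centre that stopped reporting at 1 year would break those provisions. The case report form is not shown and may list all 13 complications at every visit.

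Much of this stands. That the range bounds reporting is an inference from the section heading and the form-submission sentence that follows. Nor can adverse-event reporting be called the only route for the nine complications; it is the main one the article describes. What the defence does not remove is the conflict. No other end of the adverse-event period is given, Table 3's row names only four complications, and its last column is labelled 3 years.

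Three stronger readings are tempting and are not supported:

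- **That recurrence goes unreported in year 2.** Symptomatic recurrence is a serious event, the serious-event section sets a 24-hour limit with no calendar stop, and the 2-year visit records recurrence with its date.
- **That the comparison of arms is biased.** Randomisation is in blocks within centres, so early stopping by centre or calendar should fall about equally on both arms. Bias would need follow-up that differs by arm, which nothing in the document shows.
- **That a particular number of events will be lost.** Any such number rests on assumed rates and stopping shares.

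**Conclusion.** The point holds in a limited form. The AE reporting section's variable end conflicts with a complication outcome fixed at 2 years for every patient, and nine of the 13 complications depend mainly on that reporting as the article describes it. The consequence is possible under-counting and 2-year rates that are not comparable across patients or with other trials. It affects a secondary outcome. The χ² or Fisher comparison should stay about valid under the null hypothesis if the shortfall is balanced by the centre-stratified randomisation.

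The size cannot be derived from the documents. It would be small if most of these complications occur early, which is plausible but not stated. The calendar result, that only about 48% could reach 2 years by June 2020, assumes uniform accrual. It shows that unequal observation is likely in practice and does not come from the AE reporting wording alone. The correction is worth making, with moderate priority.

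**What to change.** 1. In AE reporting, replace the range with one end of adverse-event reporting for all patients: 2 years after surgery. Give it as a time and not as Visit 7 until Table 3's 3-year heading is reconciled with the 2 years used elsewhere. This is a change of wording; the 2-year call is already scheduled.
2. Reconcile three further places with that end: the last column of Table 3, the rule that 1 year of data makes a complete case, and the end of data collection in June 2020. Two years after a last recruitment in December 2019 is December 2021, 18 months later. Either the calendar is extended, which has a real cost, or the article says that 2-year rates will rest on incomplete follow-up.
3. In the 2-year complication comparison, count patients with shorter follow-up to their last contact and not as event-free at 2 years, for example with a cumulative-incidence estimate at 2 years. This needs event dates and last-contact dates, and an addition to the χ² or Fisher test; the detail can go in the statistical analysis plan.

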### Serious adverse event emergency reporting

Reporting time limit for SAE will be within 24 hours of onset. Any SAE will be continuously monitored and reported until it is healed, stabilises or recovers to near baseline conditions, irrespective of whether patients have terminated or completed treatment. Any follow-up information regarding SAE will be reported within 24 hours.

### Patient completion/withdrawal from clinical study

Patients for whom the whole clinical data of at least 1 year are collected will be considered as complete cases. Patients with any one or more of the following criteria will be considered withdrawn from the study: mistakenly recruited, withdrawal of informed consent, on the request of the sponsor for safety reasons or patient conflicts or lost to follow-up. The date and reasons for withdrawal will be recorded on the eCRF. After termination of the study, the data collected at the last visit will be evaluated, except for data from those lost to follow-up.

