### Methods/Design

#### Study design

This is a prospective, large-sample, multicentre, randomised controlled trial that will include a cohort of over 720 patients with inguinal hernia. The trial committee organisation and contributions and role are provided in the see online supplementary file 1. In strict accordance with the Consolidated Standards of Reporting Trials standards,^16^ the baseline data (preoperative data), therapeutic regimen, therapeutic outcome and medical costs during hospitalisation of patients with inguinal hernia will be recorded. Patient data will be collected using an electronic data capture system (EDC).

10.1136/bmjopen-2017-016481.supp1Supplementary file 1

According to recommendations for treatment and follow-up of inguinal hernia repair in adults in the Guidelines for the Diagnosis and Treatment of Inguinal Hernia in Adults (2014 Edition) formulated by Chinese scholars^17^ and the Adult Inguinal Hernia Treatment Guidelines (Updated Edition in 2014) developed by the European Hernia Society,^18^ patients who undergo herniorrhaphy will be followed up at seven time-points: at baseline (at admission, visit 1), predischarge and at 1 week (visit 2), 1 month (visit 3), 3 months (visit 4, clinic visit or telephone follow-up), 1 year (visit 5, telephone follow-up) and 2 years after surgery (visit 6, telephone follow-up). The flow chart of the study protocol is shown in figure 1. Prior to surgery: patients will be rescreened against inclusion and exclusion criteria. Signed informed consent will be obtained. Patient’s demographic data, history of disease and medication and admission condition and vital signs will be recorded. Clinical examination data will be collected from each centre, including history of disease, physical examination, laboratory testing results, imaging findings, preoperative VAS pain score, intraoperative findings and details of occurrence and management methods of intraoperative injury to the intestinal tract and bladder, spermatic cord and vascular system.

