### Randomisation and blinding

This study is a multicentre trial, so stratified block randomisation will be performed in each centre. A randomisation sequence table will be generated by a statician who will not be involved in the trial using Statistical Analysis System (SAS V.9.1). The serial numbers assigned to each patient will be preserved in opaque sealed envelopes. The sealed envelopes will be subsequently given to the trial centre. All patients will not know the surgical regimen until after the surgery. The surgeons will not be blinded to the surgical regimen. Outcome assessors will be blinded to the surgical records in the electronic case report form (eCRF).

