#### Preperitoneal space repair

The skin will be cut and subcutaneous tissue will be dissected. The abdominal external oblique aponeurosis will be dissected along the fibres. The abdominal internal oblique aponeurosis and transversus abdominis muscle will be bluntly separated to expose the transverse fascia. Dissociation of the hernia sac will be done as described above in the anterior transversalis fascia repair.

Transabdominal preperitoneal or totally extraperitoneal laparoscopic techniques were used to dissociate preperitoneal space, strip spermatic cord peritoneum, anatomise and expose the pubic pore. A polypropylene patch will be placed in the prevesical space and Bogros’ space to achieve repair of the pubic pore-containing area.

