### Outcome measures

#### Primary outcome measure

To reduce the outcome bias of a single evaluation, the incidence of chronic pain at 1 and 2 years after surgery will be evaluated. According to International Association for the Study of Pain, VAS pain score >0 for over 3 successive months indicates chronic inguinal pain.^20^

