### Statistical analysis

Statistical analysis will be performed by a statician using SPSS V.19.0 software (SPSS). Continuous variables will be statistically described using the mean, SD, median, minimum and maximum. The categorical variables will be expressed using numbers and percentages.

The analysis will be performed on the basis of the intention-to-treat principle. Descriptive statistics of baseline information will be performed. The χ^2^ test or Fisher's exact test will be used for analysis of categorical variables, such as the incidence of postoperative chronic pain (primary outcome measure) and the incidence of postoperative complications (secondary outcome measure) between groups. Independent sample t-test or Mann-Whitney U test will be used for comparisons of continuous variables, such as SF-36 score, between groups. Cost-utility analysis will be used for economic evaluation, and sensitivity analysis of cost and utility will be performed.

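### Mistaken recruitment counts as withdrawal with no limit to pre-randomisation facts, so the intention-to-treat analysis of the primary outcome can lose randomised patients

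*Protocol article*

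**What the plan says.** All references are to the protocol article.

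- *Patient completion/withdrawal from clinical study*: "Patients with any one or more of the following criteria will be considered withdrawn from the study: mistakenly recruited, withdrawal of informed consent". The list goes on to sponsor requests and loss to follow-up. No time point is attached to mistaken recruitment, and nothing says who decides or whether that person knows the arm.
- Same section, on completeness: "Patients for whom the whole clinical data of at least 1 year are collected will be considered as complete cases". On data from patients who stop: "After termination of the study, the data collected at the last visit will be evaluated, except for data from those lost to follow-up".
- *Statistical analysis*: "The analysis will be performed on the basis of the intention-to-treat principle". No exception is made for patients found to be ineligible.
- *Randomisation and blinding*: "The surgeons will not be blinded to the surgical regimen".
- *Study design*: before surgery, "patients will be rescreened against inclusion and exclusion criteria". The Visit 1 list repeats this check and includes imaging and hernia classification.
- *Primary outcome measure*: "the incidence of chronic pain at 1 and 2 years after surgery will be evaluated". Chronic pain is a VAS above zero lasting more than three successive months.
- *Study flowchart* and *Follow-up*: VAS is listed at Visit 1, then at 1 year and 2 years, and at no visit between.

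**The concern.** An eligibility error can come to light before or after randomisation. Stopping a patient before randomisation harms nothing. Stopping one afterwards removes a randomised patient from the comparison, and the withdrawal section does not separate the two cases.

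Intention to treat needs an outcome, or a defensible substitute for one, from every randomised patient. A rule that ends follow-up for some of them works against the analysis principle stated in the next section. Because people who know the arm are in a position to raise the eligibility question, the rule also leaves room for exclusions that are not balanced. At stake is the protection that randomisation gives to the primary comparison of chronic pain.

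**Working it through.** The plan gives no figure for mistaken recruitment, so there is none to reproduce. The check has two parts: whether the rule can remove the primary outcome, and what would be needed for bias.

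**Part 1. Can the outcome be recovered after withdrawal?**

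1. Suppose a patient is randomised, judged mistakenly recruited around the time of surgery, and withdrawn. Assume that withdrawal ends visits, which is the ordinary meaning and fits the rule on using the last visit.
2. VAS data held at that point: the Visit 1 score only.
3. VAS data needed: 1 year and 2 years.
4. Last-visit rule: the last available visit is Visit 1, the predischarge visit or an early follow-up visit. Visit 1 gives a preoperative score, and no VAS is listed for the others. A preoperative score cannot show chronic pain after surgery.
5. The patient is not a complete case either, because less than one year of data exists.

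So the patient is in the intention-to-treat population by principle but has no observed primary outcome.

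**Part 2. When would this bias the comparison?**

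Let *p* be the true pain risk in an arm, *w* the fraction withdrawn from that arm only, and *r* the pain risk among those withdrawn. The observed risk is

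(p − w·r) / (1 − w), so the bias is w·(p − r) / (1 − w).

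The bias is zero when w = 0 or r = p. If withdrawals are equal in number and kind in both arms, the two shifts cancel when the true risks are equal. Bias under no true difference therefore needs withdrawals that are unequal between arms and related to pain.

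The table below is an illustration with assumed *w* and *r*, not an estimate. It takes 10% true risk in both arms (the plan's figure for the anterior arm) and 1:1 allocation, which is an assumption. After the plan's 20% loss there are 360 × 0.8 = 288 per arm, and 288·(1 − w) in the arm with extra withdrawals. Type I error is the normal approximation for the two-sided 5% pooled test.

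| w | r | Observed risk | Bias (points) | Type I error |
|---|---|---|---|---|
| 2% | 20% | (0.10 − 0.004)/0.98 = 9.8% | −0.2 | 5.1% |
| 5% | 10% | (0.10 − 0.005)/0.95 = 10.0% | 0 | 5.0% |
| 5% | 20% | (0.10 − 0.010)/0.95 = 9.5% | −0.5 | 5.5% |
| 5% | 30% | (0.10 − 0.015)/0.95 = 8.9% | −1.1 | 7.1% |
| 10% | 5% | (0.10 − 0.005)/0.90 = 10.6% | +0.6 | 5.6% |
| 10% | 20% | (0.10 − 0.020)/0.90 = 8.9% | −1.1 | 7.2% |
| 10% | 30% | (0.10 − 0.030)/0.90 = 7.8% | −2.2 | 14.7% |

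The result runs from nothing to serious, and the documents do not say where the trial would fall.

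**The case against.** **Eligibility is a preoperative matter here.** The hernia is diagnosed, imaged and classified at Visit 1, and patients are rescreened before surgery. On this reading, mistaken recruitment means failing those checks at entry, which is rare and does not depend on the arm. This is a fair reading and probably the intended one, but the text does not say so. An error that escapes rescreening is just the case the criterion would catch.

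**Data are kept, and analysis sets belong in the statistical analysis plan.** The withdrawal section does say that last-visit data will be evaluated, and the interim analysis section mentions a full analysis set. How ineligible patients enter that set can properly be left to the analysis plan. Ending their follow-up, however, is a protocol rule, and an analysis plan can only impute what was never collected.

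**Pain is said to be recorded at every visit.** The text below Figure 1 does list pain at predischarge and at every later time point, although the visit lists and Table 3 place no VAS between baseline and 1 year. Even if pain were recorded early, a patient withdrawn around surgery could not meet or fail a definition needing more than three months of pain, assessed at 1 and 2 years.

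**A stronger reading that does not stand.** A reader might infer that the operation reveals different facts in each arm, since the preperitoneal section says "Transabdominal preperitoneal or totally extraperitoneal laparoscopic techniques were used to dissociate preperitoneal space" while the anterior repair is open, and that withdrawals will therefore depend on the arm. The documents do not support this. Intraoperative findings are recorded, but nothing makes them a trigger for withdrawal. Nothing describes inspection of the other groin, and that laparoscopy would reveal a second hernia is outside knowledge. No difference by arm is documented for hernia size or for primary status. The anterior repair also exposes the inner ring and follows the sac to its neck.

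**Conclusion.** The point holds in a limited form. The protocol states a withdrawal rule that is not confined to pre-randomisation facts and not decided blind to arm, and this conflicts with its own commitment to intention to treat. For a patient withdrawn around surgery, the primary outcome would not exist and the last-visit rule could not replace it. This rests on one assumption: that withdrawal ends follow-up.

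The rule permits exclusions that could differ by arm. It is not shown that they will differ, that operative findings would cause them, or that those withdrawn would have unusual pain risk. No rate is given, so no magnitude can be attached. The table in the working shows only what imbalance and a link with pain would have to look like before the test was affected. The correction is worth making because the rule is easily reworded and the bias, if it arose, could not be repaired afterwards.

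**What to change.** In the section on completion and withdrawal:

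1. Remove mistaken recruitment as a reason to stop follow-up. Withdrawal of consent stays.
2. State that an eligibility error found after randomisation is recorded as a protocol deviation, with its date and the information on which it rests.
3. State that these patients remain in the scheduled 1- and 2-year follow-up unless they withdraw consent, and are analysed in their randomised arm.
4. If a sensitivity analysis excluding them is wanted, base each exclusion only on facts fixed before randomisation, judged by someone blind to arm.

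The cost is a sentence or two and a deviation code on the electronic case report form, which already takes the date and reason for withdrawal. The 1- and 2-year contacts are telephone calls already in the schedule. The downside is that a few patients who do not strictly meet the criteria remain in the primary analysis.
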